### Objectives of current study

The main objective of the current trial is to examine whether the implementation of a 15-minute rope skipping activity at the start of PE lessons would increase secondary school students’ percentage of time spent in MVPA during their classes. Changes in autonomous and controlled forms of motivation towards PE, as secondary outcomes, will also be used to evaluate the effectiveness of the intervention. The intervention will be implemented by the PE teachers, assisted by rope skipping ambassadors provided to schools [12]. The main roles of ambassadors will be to assist teachers in running the classes, demonstrate rope skipping skills taught by the teacher, and to ensure teachers adhere to the structured plan provided to them during the training. As the intervention will be delivered at the class level, a cluster (i.e., class) randomized controlled trial was considered to be the most appropriate study design. Specifically, the intervention will be implemented in classes assigned to the experimental group for four consecutive lessons. While teachers of classes allocated in the control (i.e., delayed intervention) group will employ usual teaching practices during the experimental period. We hypothesize that students’ autonomous motivation towards PE would predict higher percentages of time spent in MVPA during PE classes. Furthermore, after controlling for students’ autonomous motivation and perceived autonomy support from their teachers, students in the experimental group, compared to those in the control group, will spend higher percentages of time in MVPA during three lessons when the intervention is applied.

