#### Secondary outcomes

Secondary outcomes include students’ time spent in sedentary, light, moderate, and vigorous physical activity as measured by accelerometry, and defined using Evenson et al.’s [25] cut-points. Perception of autonomy support provided by their teachers during the last four PE lessons, and their motivation (autonomous and controlled) during the last four PE lessons were also measured as secondary outcomes. Psychological variables will be measured using self-reported questionnaires administered using pen and paper at the end of Lesson 4 (baseline) and Lesson 8 (post-test). Specifically, the 6-item version of the Learning Climate Questionnaire [28] will be used to measure students’ perceived autonomy support provided by their teachers. The original scale in English was translated into Chinese using a back-translation protocol. As the translated scale has not previously been used, factorial validity of responses will be examined before the main analyses are conducted. In terms of motivation orientations, the Chinese Perceived Locus of Causality Questionnaire (PLOCQ) [29] will be used to measure autonomous and controlled motivation. Evidence of validity and reliability of the scale scores has been shown by Lonsdale et al. [29]. As motivational factors are likely to differ across individuals, students’ motivation towards PE was considered as a variable at the individual level. In contrast, as perceived autonomy support is referenced to the same teacher, the mean scores within each cluster will be aggregated to form an indicator representing this construct at the cluster level.

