### Statistical methods

Multilevel modeling will be used to account for the effects of participant clustering. Specifically, a three-level (time within student within class) model will be examined. For our primary outcome of students’ percentage time spent in MVPA, the effects of group allocation and student gender on percentages of time spent in MVPA will be examined using a multilevel regression model. The group × gender interaction effect will also be examined to determine whether the effect of the intervention is homogeneous across genders. Further, we will also examine a model by adding perceived autonomy support, autonomous and controlled motivation as potential confounders of the outcome. Two-tailed tests with an alpha level of .05 will be used to determine the significance of all results. To examine whether the intervention would lead to changes in motivation variables and perceived autonomy support by teachers, these variables will be regressed on group, gender, and group × gender in an additional series of three-level regression analyses. Statistical analyses of the study will be conducted by a statistician blinded to the hypotheses of the study and to each class’ allocation to the experimental or control condition.

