Based on our knowledge, this is the first intervention designed specifically to increase students’ MVPA during PE lessons in space confined environments. Apart from MVPA, we proposed to simultaneously examine the effects of the intervention on students’ autonomous and controlled motivation towards PE, as specified by SDT [14]. Based on the theory, these outcomes have important ramifications to students’ future engagement in PA, and also their physical and psychological well- and ill-being. Accordingly, we hypothesize that the intervention would increase students’ MVPA during PE, and also support more adaptive forms of motivation. In this study we also proposed to measure the perceived autonomy support and control by PE teachers. Within SDT, these perceptions are important predictors of students’ motivation towards PE, and in turn the amount of MVPA they engage in class. Our study will provide preliminary evidence on the relation between perceived teacher behaviors and students’ objectively measured activity levels. Further, our results could inform future research directions in terms of methods to further improve PE intervention effectiveness. For instance, future work could investigate whether the intervention could also further enhance students’ autonomous motivation if teachers were given training to be more autonomy supportive [33]. In conclusion, the results from our study may advance both teaching practices and theory alike.

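### Motivation and autonomy support, themselves trial outcomes, enter an additional MVPA model as confounders without a baseline restriction, and the group hypothesis is worded conditional on two of them

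*Protocol article*

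**What the plan says.** All references are to the protocol article.

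- **Statistical methods, model structure:** "a three-level (time within student within class) model will be examined".
- **Statistical methods, first MVPA model:** "the effects of group allocation and student gender on percentages of time spent in MVPA will be examined using a multilevel regression model". An interaction between group and gender is examined as well. No psychological variable is in this model.
- **Statistical methods, additional MVPA model:** "we will also examine a model by adding perceived autonomy support, autonomous and controlled motivation as potential confounders of the outcome". The measurement occasion is not given.
- **Statistical methods, next analysis:** "To examine whether the intervention would lead to changes in motivation variables and perceived autonomy support by teachers", the same variables are regressed on group, gender and their interaction.
- **Secondary outcomes, status:** perceived autonomy support and "their motivation (autonomous and controlled) during the last four PE lessons were also measured as secondary outcomes".
- **Secondary outcomes, timing:** the questionnaires are "administered using pen and paper at the end of Lesson 4 (baseline) and Lesson 8 (post-test").
- **Primary outcome, timing:** post-test accelerometry is taken in Lessons 5 to 7.
- **Objectives of current study:** the main objective is whether the rope skipping activity raises the percentage of lesson time in MVPA, with no conditioning. The group hypothesis in the same section is stated as holding once account is taken of "autonomous motivation and perceived autonomy support from their teachers, students in the experimental group, compared to those in the control group".
- **Discussion:** the intervention is expected to raise MVPA "and also support more adaptive forms of motivation". Perceived teacher behaviour is described as acting on motivation, and motivation in turn on MVPA.

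**The concern.** In a randomised comparison a confounder has to precede allocation. A variable that allocation can change is an outcome, and if it also influences MVPA it is a mediator. The article gives the same three variables both roles: covariates of the group effect on MVPA, and outcomes of group. Its own theory puts motivation on the path to MVPA.

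If scores taken after the intervention enter the model, the group coefficient loses whatever part of the effect runs through motivation or teacher climate. It can also pick up bias from unmeasured causes shared by the score and MVPA. The Lesson 8 questionnaire has a further difficulty: it is completed after the MVPA it would adjust, so it may partly be a consequence of how active the student was.

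What is at stake is which coefficient answers the trial's main question. Statistical methods describes two MVPA models and names neither as primary. If they disagree, the hypothesis as worded in the Objectives section directs the reader to the adjusted one.

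**Working it through.** **1. The plan's own figure.** The only planned effect size is d = 1.0 (Sample size), used below as a yardstick. The calculation built on it reproduces:
- Two-sided t-test, alpha 0.05: 17 per arm gives power 0.807 and 16 per arm gives 0.781, hence 34 students.
- Design effect: 1 + (7 − 1) × 0.63 = 4.78.
- 34 × 4.78 = 162.52, rounded up to 163. 162.52 / 7 = 23.2, rounded up to 24 classes, or 24 × 7 = 168 students.

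The present point does not depend on these numbers.

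**2. Order of events.**
- Lessons 1 to 3: baseline MVPA.
- End of Lesson 4: baseline questionnaire. Randomisation follows the baseline measures, and the teacher workshop falls between Lessons 4 and 5.
- Lessons 5 to 8: intervention. Post-test MVPA is recorded in Lessons 5 to 7.
- End of Lesson 8: post-test questionnaire, which asks about the preceding four lessons, that is Lessons 5 to 8.

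Lesson 4 scores therefore precede allocation. Lesson 8 scores follow both the intervention and the post-test MVPA.

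**3. Two possible readings of the additional model.**
- *Lesson 4 scores only.* The covariates cannot be affected by allocation. The group coefficient still targets the total effect, and the adjustment is legitimate.
- *Scores at both occasions, matched to the MVPA periods.* This is the natural form when time is the lowest level and each score is measured once per period. It brings in Lesson 8 scores. The group coefficient then equals the total effect only if the intervention leaves the scores unchanged or the scores are unrelated to MVPA given group.

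The text does not choose between the two.

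**4. Illustration of size, on assumed inputs.** None of the inputs below is in the documents.

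Let a be the shift the intervention causes in a score and b the slope of MVPA on that score. With no shared unmeasured cause, conditioning on the post-test score removes a × b from the total effect:
- a = 0.3 SD, b = 0.2: 0.3 × 0.2 = 0.06, leaving 0.94 of 1.0.
- a = 0.5 SD, b = 0.4: 0.5 × 0.4 = 0.20, leaving 0.80 of 1.0.

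A single-level linear simulation with the total effect set to 1.0 adds an unmeasured common cause with coefficient 0.5 on both score and MVPA in half of the settings. It uses a of 0, 0.2 or 0.5 (units of the simulated score) and b of 0, 0.2 or 0.4:
- Unadjusted, or adjusted for the baseline score: 1.0 throughout, to within 0.01.
- Adjusted for the post-test score, a = 0: 1.00 throughout.
- Adjusted for the post-test score, a = 0.2: 1.00 down to 0.85.
- Adjusted for the post-test score, a = 0.5: 1.00 down to 0.62.

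The direction is built in, because the common cause was given the same sign on both variables. With opposite signs that component would push the estimate the other way.

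**5. Objective against hypothesis.** The main objective asks for the effect of introducing the activity, and the abstract evaluates effectiveness by comparing changes in MVPA between groups. Neither conditions on anything. The group hypothesis in the Objectives section conditions on autonomous motivation and autonomy support. With Lesson 8 scores, objective and hypothesis refer to different quantities.

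**The case against.** A reader might infer that the plan enters post-test scores and that its treatment estimate is therefore biased. The documents do not support that, for four reasons.

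- **The occasion is unstated.** Nothing says that Lesson 8 scores are the covariates. Time-varying entry is an inference from the three-level structure and the two questionnaire occasions. A condensed article may leave the occasion to a fuller document. This stands as a limit on the claim. It does not remove the point, because the article labels trial outcomes as confounders and ties its hypothesis to the adjusted model.
- **The model is additional.** The first MVPA model omits all three variables and its estimate is untouched. This stands in full.
- **Not all three variables are meant to move.** Only autonomous motivation is clearly expected to improve. Controlled motivation is meant not to rise, and training teachers in autonomy support is left to future work. A score that does not move causes no such bias. This also stands, although the plan tests all three for a group effect.
- **Motivation as a predictor.** It would go too far to say that motivation is tested as a predictor measured after the outcome. Lesson 4 motivation against Lessons 5 to 7 MVPA fits the stated schedule, and no section ties that hypothesis to Lesson 8.

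The size is also wholly assumed, as the working shows.

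**Conclusion.** The point holds in a limited form. The article calls three secondary outcomes confounders in an additional MVPA model and does not restrict them to baseline. The most natural implementation would include scores recorded after the intervention and after the outcome. If the intervention moves those scores, the adjusted group coefficient need not be the total effect. The 0.06 to 0.20 SD range, and the fall to 0.62 in the simulation, show only that the gap could matter against d = 1.0. They do not estimate it.

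Separately, and whichever scores are used, the conditional wording of the group hypothesis does not match the unconditional main objective. This makes the matter more than a missing detail: following the Objectives and Statistical methods sections as written can tie the trial's main claim to a coefficient that does not answer its main question. It should be settled before analysis.

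**What to change.** 1. In Statistical methods, name the MVPA model without post-randomisation covariates as the primary analysis.
2. In Objectives, reword the group hypothesis as the total effect of allocation on MVPA, without conditioning on motivation or autonomy support.
3. In any adjusted MVPA model, restrict autonomous motivation, controlled motivation and class-mean autonomy support to their Lesson 4 values, and call them baseline covariates instead of confounders.
4. Test whether motivation predicts MVPA with Lesson 4 motivation against Lessons 5 to 7 MVPA.
5. Keep Lesson 8 scores for their own outcome models. Label any MVPA model that uses them as exploratory mediation, and note that they were recorded after the MVPA.

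The cost is wording only. The Lesson 4 questionnaire is already in the schedule, and no additional measurement or change in sample size is needed.

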### Outcomes

#### Primary outcome

The primary outcome of the study is the proportion of PE lesson students spend in MVPA. This will be measured using ActiGraph (Pensacola, Florida) GT3X + accelerometers. MVPA will be defined using Evenson and colleagues’ criteria [25], and 1-second epochs will be used [26]. Evenson et al.’s cutoff values were chosen because they were found to be more accurate than other commonly used cut points [27]. To test the validity and sensitivity of the devices of capturing non-lateral movements such as rope skipping, we invited 12 boys and girls with varying rope skipping experience perform rope skipping tricks (in 1-minute bouts with at least one minute rest in between) that will be included in the intervention while wearing accelerometers. For all skippers and for all tricks tested, the activity was classified as MVPA based on Evenson et al.’s cut points. In our formal trial, accelerometry measurements will be taken during the first three lessons at baseline (Lessons 1 to 3; see Figure 2). MVPA will be measured for the same sets of seven students in each class throughout the study. These students will be randomly selected by the investigators from class lists (not containing names of students) provided by teachers using a random number generator. The mean of each student’s proportion of time spent in MVPA during these three classes will be used as his or her baseline. The primary outcome will pertain to the individual level and will not be aggregated within the cluster.

After baseline assessments, classes will be randomized into either the experimental or the control group. Teachers of classes in the experimental group will be invited to attend the teacher workshop after Lesson 4, and before Lesson 5. Following the workshop, these teachers will implement the intervention in their class for four consecutive PE lessons (Lessons 5 to 8). For schools in the control group, teachers will conduct classes using their usual methods, which are not expected to include rope skipping. Post-test accelerometry measures will be taken during Lessons 5 to 7. The mean of each student’s MVPA percentages taken from these three classes will be used as follow-up scores. Similarly, this measure pertains to the individual level.

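### Two-tailed .05 is applied to seven secondary outcomes and four gender interactions with no adjustment, order or exploratory label, although motivation results are used to judge effectiveness and the gender test is too weak to show homogeneity

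*Protocol article*

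**What the plan says.** All places are in the protocol article.

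- **Statistical methods:** "Two-tailed tests with an alpha level of .05 will be used to determine the significance of all results". No adjustment or testing order follows.
- **Primary outcome:** one is named. "The primary outcome of the study is the proportion of PE lesson students spend in MVPA".
- **Secondary outcomes:** "Secondary outcomes include students’ time spent in sedentary, light, moderate, and vigorous physical activity as measured by accelerometry". The same paragraph adds perceived autonomy support, autonomous motivation and controlled motivation, so there are seven.
- **Objectives of current study:** "Changes in autonomous and controlled forms of motivation towards PE, as secondary outcomes, will also be used to evaluate the effectiveness of the intervention".
- **Discussion:** a directional hypothesis covers motivation as well as activity: "we hypothesize that the intervention would increase students’ MVPA during PE, and also support more adaptive forms of motivation".
- **Statistical methods, on gender:** "The group × gender interaction effect will also be examined to determine whether the effect of the intervention is homogeneous across genders". The same interaction term is also written into the models for the three psychological variables, which makes four interactions. None is written for the four activity bands.

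Two places pull the other way. The Background section on motivational determinants describes a successful intervention as one that raises activity, promotes autonomous motivation and does not raise controlled motivation. The Discussion speaks of exploring the gender question.

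**The concern.** The .05 rule is a positive statement about every result, not a detail left open. An analysis plan that adjusted or ordered the secondary tests would have to override it.

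An unadjusted .05 does little harm when secondary outcomes are only descriptive. Here two of them are assigned a part in judging effectiveness, and a hypothesis is stated for them. The rule lets each be called significant on its own, whatever MVPA shows, and it gives the activity bands and autonomy support the same standing. A reader of the results could not tell which significant secondary findings were protected against chance.

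The gender interaction has the opposite weakness. It is given the task of deciding whether the effect is homogeneous, at a sample size set for the main effect. A non-significant result could then be reported as evidence that boys and girls respond alike.

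**Working it through.** **1. The plan's own figure.** Inputs from Sample size: d = 1.0, two-tailed alpha .05, power .80, ICC .63, seven students per class.

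- The two-sample t-test needs 16.7, so 17 per arm and 34 in total (power .807), as stated.
- Design effect: 1 + (7 − 1) × .63 = 4.78. Then 34 × 4.78 = 162.5, so 163 students; 163/7 = 23.3, so 24 classes and 168 students, as stated.

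This uses .05 for one test. The primary error rate and the sample size are therefore not in question.

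**2. Counting the tests under the .05 rule, beyond the primary contrast.**

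- Motivation outcomes named for judging effectiveness: 2.
- Secondary group effects: 4 activity bands + 3 psychological variables = 7.
- Gender interactions on secondary outcomes: 3. The fourth is on MVPA, the primary outcome.

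**3. Chance of at least one false positive with no true effect.** For k independent tests it is 1 − .95^k:

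- k = 2: 1 − .9025 = .0975
- k = 7: 1 − .6983 = .302
- k = 10: 1 − .5987 = .401

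The document gives no correlations between outcomes, so common values of 0, .5 and .8 are assumed and simulated with correlated null z-tests. Group effects and interactions are treated as two mutually independent blocks, because the average group effect and the interaction are uncorrelated in a balanced design.

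| Family | 0 | .5 | .8 |
|---|---|---|---|
| Two motivation outcomes | .10 | .09 | .08 |
| Three psychological outcomes | .14 | .13 | .10 |
| Seven secondaries | .30 | .23 | .15 |
| Seven + three interactions | .40 | .33 | .23 |

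Example for the last cell: the blocks give .148 and .098, so 1 − .852 × .902 = .23. If all ten tests shared a correlation of .8 across blocks as well, the figure would be .17. If the four activity bands are made to sum to a constant, because they share one lesson, the seven-outcome figure is about .27 to .29.

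**4. Power of the group × gender test on MVPA.** Schools are eligible only with a unisex PE policy (Participants), and classes are matched on class gender (Sequence generation). Gender is therefore taken as a class-level factor. An even split of 12 boys' and 12 girls' classes is assumed, giving four cells of six. Units are the standard deviations of the planned d.

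- Variance of a class mean: 4.78/7 = .683.
- Main-effect SE: √(.683 × 2/12) = .337.
- Interaction SE: √(.683 × 4/6) = .675, twice the main-effect SE.

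Power is from the noncentral t with 24 − 4 = 20 df. An assumed correlation r with baseline multiplies the SE by √(1 − r²); for r = .7 that is .714, giving .482.

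| Setting | SE | Power, difference 1.0 | Power, difference 0.5 |
|---|---|---|---|
| ICC .63, no baseline adjustment | .675 | .29 | .11 |
| ICC .63, baseline r = .7 | .482 | .51 | .17 |
| ICC .30 (assumed), no baseline adjustment | .516 | .45 | .15 |

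A between-gender difference of 1.0 is as large as the whole planned effect. With SE .675 the 95% interval for the interaction is about ±2.09 × .675 = ±1.41; with SE .482 it is about ±1.01. Neither excludes important heterogeneity when the estimate is near zero.

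**The case against.** The strongest reply is that the hierarchy that matters is already there. One outcome is primary, the rest are called secondary, and the Background describes success as a joint condition that includes a rise in activity. A joint condition does not inflate the chance of declaring success. Secondary multiplicity is also commonly left to the analysis plan, and the Discussion calls the gender question something to explore.

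Much of this stands, and it rules out several stronger readings that a reader might infer:

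- *A false secondary finding is likely.* Not supported. The chance passes one half only with 14 independent tests (1 − .95^14 = .51), which needs an interaction for every secondary outcome. The protocol writes three.
- *There is no hierarchy at all.* Not supported. What is missing is an order, adjustment or label among the secondaries.
- *A trial with null MVPA would be declared a success on any one secondary.* The Background description points against this. It is not carried into Statistical methods as a decision rule, however, so separate motivation claims remain open.
- *The figure is .43.* That counts the MVPA interaction, which is not a secondary outcome.

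For the two outcomes actually named for judging effectiveness, the inflation is modest, at about 1.6 to 2 times .05. It is also fair that a power of .29 gives no credit for baseline data or for matching on baseline MVPA, and that it rests on class-level gender with an even split.

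The appeal to an unseen analysis plan does not stand, because the article fixes .05 for all results. Calling the gender question exploratory in the Discussion does not change the operative section, which gives it the same significance rule and a decision to make.

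**Conclusion.** The concern holds in a limited form. Secondary error is uncontrolled by a stated rule: about 8–10% for the two motivation outcomes, 15–30% for seven secondaries, and 23–40% with the three secondary-outcome interactions. These ranges rest on assumed correlations of .8 down to 0 and on no true effect anywhere. The primary test's error rate and the sample size are sound on this point.

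The gender interaction cannot establish homogeneity. Its power for a difference as large as the planned effect is about .29 at the protocol's own ICC without baseline adjustment, and about .5 with an assumed baseline correlation of .7. For a difference of 0.5 the values are .11 and .17. They assume class-level gender and equal numbers of boys' and girls' classes. No document figure supports a particular gain from baseline data or matching, so these are a range and not a prediction.

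**What to change.** In Statistical methods:

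1. Limit the unadjusted two-tailed .05 rule to the primary MVPA contrast.
2. Test autonomous and controlled motivation with Holm at a family-wise .05: the smaller p-value against .025 and, if that passes, the larger against .05. Holm is preferable to a fixed sequence after MVPA, which would leave a rise in controlled motivation untested whenever an earlier step failed.
3. State that a claim of effectiveness also requires the MVPA result, as the Background already describes.
4. Report the four activity bands, perceived autonomy support and all group × gender terms as exploratory, with estimates and 95% confidence intervals.
5. Replace the aim of deciding whether the effect is homogeneous with reporting the interaction estimate and its interval, and say that a non-significant interaction will not be read as homogeneity.

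The cost is a few sentences. Sample size and data collection do not change. The motivation tests lose a little power: by the normal approximation, a test with power .80 at .05 has .71 at Holm's stricter first step. The remaining secondaries can no longer support confirmatory claims.
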